### Sample size

Since the present study is a pilot study (focused primarily on understanding feasibility and refining processes in anticipation of a full-scale trial), the sample size calculation is based on a conservative assumed rate of the secondary outcome (change in suicide attempts) of 10% at the end of 12 months in the control group. Thus, a minimum enrolment of 500 participants (250 control; 250 intervention) has a power of 80% (at a 2-sided alpha level of 0.05) to detect an absolute risk reduction of 10 percent points (minimal detectable difference of 10% between the groups (intervention and control), while allowing for an expected 20% loss to follow-up over the 12 months follow-up period.

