### Outcomes

As this is a pilot study, the primary outcomes of interest are related to its implementation, specifically: reach, adoption, implementation (including cost), feasibility and acceptability, as summarized in
Table 1. The RE-AIM framework will serve as the guiding conceptual framework for the primary outcomes in this study.
^
20,
21
^ Secondary outcomes include suicidal behaviour (including intention, ideation, planning and fatal or non-fatal suicide attempt) and symptoms of depression over a 6-
and 12-month follow-up period.

**Table 1. T1:** Implementation outcomes, indicators and timepoints of data collection.

Outcome	Indicator	Data source	Data collection
**Reach**	1) Absolute number and proportion of people who agreed to join the study	Study data (Nurses records)	Process data (during study period)
	2) Participant attrition/retention rate at endline (5 sessions)	Study data (CHOs records)	
	3) Demographic characteristics of participants compared to non-participants (Refusals and Lost to Follow up cases ^1^)	Study records	
**Adoption**	Nurses: Number and % of health centres where participants were identified and recruited	Study records	Process data (during study period)
	CHOs: Number and % of trained CHOs who deliver the CASP intervention		
**Implementation**	Of intervention: Proportion of CASP sessions which were delivered as per CASP intervention delivery schedule (on time)	CHO records	Process data (during study period)
	Of training: Change in knowledge, attitudes and skills of delivery agents (CHOs)	Pre-post survey of knowledge, skills and attitudes	Pre-pilot and at 18 months (sustained impact)
	Intervention costs, costs of (healthcare) resource use and quality of life	TiC-P and EQ-5D-5L with random sub-sample of 50 participants per condition (n=100)	Baseline and 6 months follow up
**Feasibility**	Extent to which health workers felt CASP is feasible to deliver	Semi-structured interviews with a purposive sample of health workers (n=20)	After concluding participant recruitment
**Acceptability**	Extent to which participants felt CASP is acceptable	In-depth interviews with a random sample of n=20 participants per district (total n=40)	After final contact point

^1^
Lost to Follow Up refers to individuals who have provided verbal consent to nurses in emergency wards, but with whom we have not been able to make subsequent contact and so therefore have not been formally recruited into the study.

*Primary outcome measures*

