A brief survey collecting data on age, gender, education, marital status, employment status, caste/tribal background and income will be used to collect participant demographic information.

**Reach** will be measured by the absolute number, proportion, and representativeness of individuals who participate in CASP and how representative participants are compared to the target population.
**Adoption** will be measured by the absolute number and proportion of health facilities and intervention agents who are willing to initiate and carry out CASP.

**Feasibility** will be measured using semi-structured interviews exploring the perceptions of health workers and supervisors on the extent to which CASP is viable as a suicide prevention response within the health system. Within these interviews, we will also explore the feasibility of health system adoption beyond the study, e.g. what supervision pathways can be established for maintenance and scale-up of the programme (as during the pilot, supervision will be carried out by the research team).

**Acceptability** of intervention delivery will be measured qualitatively via the same interviews with health workers and supervisors specifically to assess comfort with the CASP training and intervention content. Acceptability for participants will be measured qualitatively via in-depth interviews with a random sample of n=20 participants per district (total n=40) after their last session of CASP which will explore participant comfort with CASP session content and structure and to solicit feedback for adaptations to the intervention.

**Implementation** is defined as 1) the intervention agents’ adherence to the CASP schedule of session delivery (1, 2-, 4-, 7-
and 11-weeks contact points), 2) the impact of the CASP training program and 3) the costs of the intervention. Timeliness of CASP sessions as delivered by CHOs will be measured via program data, specifically CHO records. Knowledge and skills improvement due to the CASP training will be measured by a pre-post knowledge and skills assessment with nurses and CHOs.

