### Progression criteria

To determine if this study will proceed to a randomized controlled trial, we have developed progression criteria based on recommendations put forth by Mellor et al. (2023).
^
37
^ The progression criteria is focused on assessing the feasibility of the study design and the feasibility and appropriateness of the intervention, indicated in
Table 2 below.

**Table 2. T2:** Progression criteria for primary outcomes.

Outcome	Progression criteria
Feasibility of participant recruitment	Minimum recruitment rate of 50% of eligible participants
Feasibility of intervention design	• Retention of participants: <30% loss to follow up at 6-month data collection • Retention of CHOs: <20% of CHOs discontinue delivery of CASP sessions
Intervention implementation	Delivery of the intervention judged as highly feasible and acceptable by health workers and participants through qualitative data

These criteria have been selected considering practical limitations and contextual factors that may challenge the feasibility of integrating CASP into the existing health system, for e.g. lack of government resources to incentivize new tasks for health workers, significant distances to be travelled between facilities and participant homes (without adequate travel compensation) for CHOs, and stigma around suicide. As this is the first integration of CASP within the existing health system, one key focus of this study is to assess the impact of practical and contextual limitations and identify where and how we can adapt the study processes to better suit low resourced public health settings (where the scope for scale-up is largest).

Red Amber Green traffic light approach
^
37

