## Discussion

This pilot study evaluates the implementation and preliminary effectiveness of a contact and safety planning (CASP) intervention delivered by trained health workers for suicide prevention in Chhattisgarh, India. While CASP has been previously tested among a refugee population in South India,
^
8
^ this study is the first to adapt and integrate CASP for an at-risk population within the public health system. By assessing the intervention’s feasibility, reach, acceptability, adoption, and early indications of effectiveness and cost, this study seeks to generate critical evidence for suicide prevention within the health system in low-resource settings.

Conducted in collaboration with the Chhattisgarh Department of Health and Family Welfare, CASP aims to address systemic challenges felt within the health system for suicide prevention in Chhattisgarh. For example, in the control districts of Mungeli and Balodabazar, while DMHP staff provide brief follow-ups and counseling for individuals who attempt suicide and present to emergency wards in district health centres, most other districts lack adequate personnel to fulfil these roles. As a result, attempted suicides often go unattended to. Additionally, nurses in emergency wards are not trained to identify and sensitively respond to attempted suicides, which can influence the care provided and medical decision-making in emergency settings.
^
38
^ Training emergency nurses and Community Health Officers (CHOs) as a key link between emergency departments—a common point of contact for individuals at risk—and the community provides a promising pathway to address these gaps.

We anticipate challenges when implementing this study. The unexpected doubling of the CHO trainee pool due to the placement of over 200 additional CHOs in district Health and Wellness Centres poses logistical difficulties for keeping to the study timeline and carrying out supervision and coordination with CHOs. Stigma around suicide within families and communities may hinder follow-ups and which are central to this model. Additionally, the lack of systematic data collection on suicide attempts and follow-ups in control districts complicates the evaluation. To mitigate this, data collectors will conduct weekly visits to engage with primary and community health centres and support in improving the consistency and quality of data collection and reporting at this level.

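### CHO adoption is a percentage of all trained CHOs, but a CHO can deliver CASP only if given a participant, so this primary outcome mixes willingness with local caseload

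*Protocol article*

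**What the plan says.** The Outcomes section states that "the primary outcomes of interest are related to its implementation, specifically: reach, adoption, implementation (including cost), feasibility and acceptability". Under the primary outcome measures, adoption "will be measured by the absolute number and proportion of health facilities and intervention agents who are willing to initiate and carry out CASP". For CHOs, Table 1 turns this into one indicator: "CHOs: Number and % of trained CHOs who deliver the CASP intervention".

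Three other sections determine who can enter the numerator and the denominator:

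- **Training:** all CHOs in the selected districts must be trained.
- **Recruitment & Retention:** the research team assigns each participant a CHO from the nearest Health and Wellness Center. No route is described by which a CHO starts a case without an assignment.
- **Discussion:** the authors report an "unexpected doubling of the CHO trainee pool due to the placement of over 200 additional CHOs".

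The planned caseload is in Sample size: "a minimum enrolment of 500 participants (250 control; 250 intervention").

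**The concern.** The definition is about willingness; the indicator is about delivery among everyone trained. The two agree only if every trained CHO has the chance to deliver. Compulsory training means that being in the denominator says nothing about willingness, and assignment by proximity means that many CHOs may never have a participant to see. Such a CHO is scored in the same way as one who was asked and refused.

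At stake is what a primary outcome can tell the team planning the next trial. A modest adoption percentage could reflect reluctance, which calls for changes to training, incentives or workload. It could equally reflect few cases per CHO, which calls for none of these. The unexpected growth of the trainee pool makes the problem worse, because it lowers the percentage without any change in CHO behaviour.

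**Working it through.** The protocol gives no target or expected value for CHO adoption, so there is no planned figure to reproduce. The check asks what the indicator would read if every CHO were willing.

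**Inputs**

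- P = 250 participants in the CASP arm (Abstract; Sample size, as part of a minimum enrolment).
- C = number of trained CHOs. This is not printed. A doubling caused by over 200 additional CHOs suggests about 200 + 200 = 400. This is an assumption, varied below.
- One CHO per participant, as Recruitment & Retention describes.

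**Formulas**

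- Ceiling, if no CHO receives a second participant: min(1, P/C).
- Expected share with at least one participant, if each case is equally likely to fall to any CHO: 1 − (1 − 1/C)^P.

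**Central case, C = 400 and P = 250**

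- Ceiling: 250/400 = 62.5%.
- Expected: 1 − (399/400)^250 = 46.5%, or about 186 CHOs.

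**Range**

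| Trained CHOs | Participants | Ceiling | Expected at full willingness |
|---|---|---|---|
| 200 | 250 | 100% | 71.4% |
| 300 | 250 | 83.3% | 56.6% |
| 400 | 250 | 62.5% | 46.5% |
| 450 | 250 | 55.6% | 42.7% |
| 500 | 250 | 50.0% | 39.4% |
| 400 | 200 | 50.0% | 39.4% |
| 400 | 300 | 75.0% | 52.8% |

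Catchments are unlikely to be equal. In a simulation with C = 400, P = 250 and gamma-distributed referral rates, the expected share fell to about 44% (coefficient of variation 0.5) and 39% (coefficient of variation 1.0).

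**What one reading could mean.** With 400 CHOs, 46.5% is what full willingness would produce on average. With 200 CHOs, about 142.9 would be expected to have a participant. The same 46.5% would then be 93 CHOs delivering, and 93/142.9 = 65% of those with a case. The percentage alone cannot separate the two situations. With CHOs asked to take a participant as denominator, and leaving aside participants who could not be reached, full willingness reads as 100% for any C and P.

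**The case against.** **No decision hangs on this percentage.** Adoption has no target, is not in Table 2 and is analysed descriptively. The absolute number is reported as well, and health workers' views are explored in interviews. This stands, and it confines the harm to interpretation. The absolute number does not solve the problem, however, because it too depends on caseload.

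**The inputs are soft.** The pool of 400 is inferred and 250 is a minimum. CHOs are also assigned after verbal consent and before written consent, and the Table 1 footnote expects some verbal consenters never to be reached, so assignments can exceed enrolments. With 400 CHOs, about 277 equal-chance assignments would already give half of them a case. It would therefore be unsafe to say that most CHOs will never be offered one. But assignments that end without contact add no delivering CHO, so they do not raise the Table 1 figure.

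**The all-trained percentage is useful.** For a programme that trains every CHO and considers scale-up, the share of the trained workforce that ends up delivering is worth knowing. Agreed: it should stay, under its own name.

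**A tempting stronger reading.** A reader might infer that the Table 2 criterion, "<20% of CHOs discontinue delivery of CASP sessions", is diluted in the same way, with CHOs who never had a case making it easy to pass. The document does not support this. A CHO can discontinue delivery only after starting it, so the natural denominator is CHOs who had started, and on that reading there is no dilution.

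**Conclusion.** The point holds for the CHO adoption indicator in Table 1. Its denominator is fixed as all trained CHOs and no section limits it to CHOs who were asked to take a participant, so it does not isolate the willingness that the text sets out to measure. It is confounded rather than uninformative: a refusal by an assigned CHO would still lower it.

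Assuming about 400 CHOs, 250 enrolled participants and one CHO each, full willingness would read as at most 62.5%, and about 46% under equal-chance referral. The exact size moves with the pool and with enrolment, but the direction does not. Any pool larger than the number enrolled caps the figure below 100%, and chance clustering of cases alone would bring a pool of 200 down to about 71%. The consequence is a primary outcome that is hard to interpret; the go/no-go rule is unaffected.

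**What to change.** In Table 1, define CHO adoption as the number of CHOs who delivered at least one CASP session divided by the number asked to take at least one participant. Count in the denominator CHOs who were approached and declined, and those passed over as unavailable. Show separately the CHOs whose only assigned participants could not be contacted, so that failed contact is not read as refusal. Keep the percentage of all trained CHOs as a coverage figure, with the number trained stated beside it.

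The cost is small but not nil. The research team must record each assignment request and its outcome. Data collection describes nurses' record books and CHO visit records but no such log, and because recruitment is already under way, earlier requests may have to be reconstructed. The new measure also depends on whom the team chooses to approach: if reluctant CHOs are quietly avoided, it drifts towards 100%. That is why those passed over must be counted. Nothing now planned is lost.

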### Data collection

Baseline demographic data—including age, gender, education, marital status, employment status, caste/tribal background, income, and contact details—will be collected by Community Health Officers (CHOs) from consenting participants. Study records will include the following: (1) record books maintained by nurses at health facilities, documenting the date, age, gender, method of attempt, verbal consent status, and, if applicable, reasons for refusal; and (2) CHO records detailing the dates and locations of participant visits to monitor adherence to the CASP intervention schedule (at 1, 2, 4, 7, and 11 weeks post-attempt).

For outcome assessments, the Columbia-Suicide Severity Rating Scale (C-SSRS) and the Patient Health Questionnaire-9 (PHQ-9) will be administered to participants in the intervention group at baseline and during follow-ups at 6 and 12 months. Within the control arm, a brief follow up survey will be administered that captures suicide re-attempt at 6 and 12 month follow up points. Data collection will be conducted by trained data collectors, who are local Master’s graduates in mental health or related fields with prior experience in the health system.

To support the cost analysis and economic evaluation, a brief cost survey (Modified TiC-P) and the EuroQol-5D-5L will be administered to a random sample of 50 participants in both the intervention and control groups at baseline and at the 6-month follow-up. Data collection will be conducted using paper-and-pencil assessments or self-administered forms, based on participant preference.

Qualitative follow-up data will be collected through in-depth and semi-structured interviews, lasting approximately one hour each. These interviews will be conducted by research team members and audio recorded with prior informed consent for transcription purposes. Acceptability interviews with participants will include a random sample selected independently of intervention completion status, ensuring the inclusion of individuals who may have dropped out of the study. See
Figure 1 for research and data collection procedures.

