^ and is recommended by the World Health Organisation (WHO) as an effective intervention to reduce suicides and attempted suicides in the general population.
^
13
^ Safety planning interventions have been found to reduce fatal and non-fatal suicide attempts in a recent meta- analysis
^
9
^ and when tested in conjunction with brief contact among veterans in the US.
^
14
^ Leveraging the public health system to deliver CASP may be a promising solution to address the treatment gap for suicide in Chhattisgarh and similarly low-resourced settings, however, the feasibility and acceptability of a health-systems approach for CASP is yet to be determined.

This study will integrate CASP into the public health system by training non-specialist health workers to identify and follow up with adults who have recently attempted suicide in two districts where the DMHP is not providing any response to suicide attempts (due to personnel shortages). We will train two groups of health workers: (1) nurses in emergency wards of health centres to identify and recruit adults who have attempted suicide from emergency wards, and (2) Community Health Officers (CHOs) at community-based Health and Wellness Centers (HWCs) to deliver the CASP intervention in the community over an 11-week follow-up period.

Follow ups by CHOs will include suicide risk assessments, provision of emotional support and empathetic listening, and collaborative safety planning to identify steps a participant can follow if they are in distress. Steps include identifying symptoms of distress, recognizing coping mechanisms and planning for future use of coping strategies, activating support networks, referrals for professional care and sharing details of the nearest emergency services. The first follow up visit will occur within one week of discharge from a healthcare facility post-attempt, and then continue periodically over the immediate 11-week period afterward.

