### Study interventions

CASP was developed specifically for individuals at risk of suicide by SNEHA Suicide Prevention Center (Chennai, India)
^
8
^ and incorporates two evidence-based components: brief contact
^
7,
11
^ and safety planning.
^
9
^ Its core focus revolves around establishing periodic connections with individuals who have recently survived suicide attempts, alongside a collaborative effort to create and track progress using personalized safety planning cards intended for distressing as well as crisis situations. Within this framework, emergency nurses will report details (name of health facility, age and gender of participant) to the project team who communicate this to Community Health Officers (CHOs) from that locality. A nearby CHO will then follow up with and visit the consenting individual at a time and place of their choosing, within the upcoming week. The timing of these visits will adhere to the contact schedule outlined in the multi-site WHO suicide study, SUPRE-MISS (1, 2, 4, 7, and 11 weeks after the attempt).
^
10,
12
^ During these visits, CHOs will extend emotional support, gauge the level of risk, and jointly work with the individual to identify personal warning signs, coping strategies, and available support mechanisms (safety planning).

Safety planning
^
8,
9
^ will be carried out by the CHO with the participant in a quiet and confidential setting after each participant has received their own safety planning card. Safety planning will be a collaborative exercise wherein the CHO will guide the participant through each step involved in safety planning and help the participant to fill in the card. Participants will be encouraged to refer to their safety planning card when they are distressed, and their use will be monitored during visits. The primary objective of the safety planning card is to support participants when they experience suicidal thoughts and urges by reminding them of coping mechanisms that make them feel better, people they can reach out to and actions they can take to make their environment safer.

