### Recruitment & Retention

Individuals presenting at district hospitals, Primary Health Centres (PHCs), or Community Health Centres (CHCs) following a suicide attempt will be identified by casualty nurses, who will screen for eligibility and invite those meeting the criteria to participate in the study. After providing a brief explanation of the study, the nurses will obtain verbal consent from interested individuals and notify the research team via telephone, sharing details such as the participant’s village of residence and hospital discharge date.

The research team will then assign a Community Health Officer (CHO) from the nearest Health and Wellness Center to follow up with the participant at a time and place of their convenience. Within one week of discharge, the CHO will meet the participant, obtain written informed consent, and initiate follow-up care as per the CASP intervention protocol.

During the informed consent process, the CHO will explain the study’s purpose, procedures, and the potential risks and benefits of participation, emphasizing that involvement is entirely voluntary. Participants will receive a consent form and an information sheet detailing the study objectives, procedures, and the contact information of CASP research team members, enabling them to seek clarifications or address concerns at any point during the study.

To support participant retention in the study, we will make up to five contact attempts over a two-week period following each scheduled follow-up appointment. These attempts will include a combination of telephone calls and in-person home visits (where feasible and safe).

If a participant misses a follow-up but can be contacted later, they will still be approached for subsequent follow-ups at later time points.

For participants who actively request to discontinue follow-ups, the study team will first explore and address any concerns to encourage continued participation. However, if the participant continues to decline, they will be formally withdrawn from the intervention and no further contact will be made.

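### The first visit may be made up to a week after discharge, but timeliness is scored in weeks from the attempt, so the on-time proportion partly reflects length of hospital stay

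*Protocol article*

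**What the plan says.** Two sections time the first visit from discharge. The Introduction states: "The first follow up visit will occur within one week of discharge from a healthcare facility post-attempt". Recruitment & Retention makes this an operating rule: "Within one week of discharge, the CHO will meet the participant, obtain written informed consent, and initiate follow-up care". The same section has nurses pass on the participant's "village of residence and hospital discharge date" to the research team, which then assigns the CHO.

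Two other sections count from the attempt. Study interventions adopts the schedule of "SUPRE-MISS (1, 2, 4, 7, and 11 weeks after the attempt". Data collection says that CHO visit dates are recorded "to monitor adherence to the CASP intervention schedule (at 1, 2, 4, 7, and 11 weeks post-attempt".

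The outcome that depends on these dates is in Outcomes, Table 1, under Implementation: "Proportion of CASP sessions which were delivered as per CASP intervention delivery schedule (on time". The text below the table defines the first element of Implementation as "adherence to the CASP schedule of session delivery" and lists the five contact points without saying which date they run from.

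**The concern.** A CHO who follows Recruitment & Retention exactly can be scored late under Data collection. The gap between the two rules is the time from attempt to discharge, which the CHO does not control. People already admitted for an attempt are eligible (Participants), and nurses report a discharge date, so the plan itself expects some stays in hospital.

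The pilot is meant to show whether CHOs can deliver the sessions on schedule. If the on-time proportion falls as stays lengthen, a low figure could be read as poor delivery when CHOs kept to their instructions. Facilities or districts with longer stays would also look worse for the same reason.

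**Working it through.** The plan states no figure for this point, so there is none to reproduce. The check is date arithmetic.

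**Inputs from the article**
- First visit due 0 to 7 days after discharge (Introduction; Recruitment & Retention).
- Contact points at weeks 1, 2, 4, 7 and 11 after the attempt (Study interventions; Data collection), so week 1 is day 7 and week 2 is day 14.
- Five sessions per participant (five contact points; Table 1).

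**Inputs assumed, because the article does not give them**
- L, the days from attempt to discharge, shown from 0 to 10.
- w, the tolerance in days, shown at 0, 3 and 7. On time means by day 7 + w.
- Compliant first visits are spread evenly over the eight days L to L + 7, discharge day included.
- Contacts 2 to 5 keep the attempt clock and are not affected by a late first visit.

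**Step 1: latest compliant first visit, day L + 7 after the attempt**
- L = 0: day 7, no conflict.
- L = 3: day 10.
- L = 7: day 14, which is the week-2 contact point.
- L = 10: day 17, past week 2.

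With L of 7 or less, both rules can be met if the CHO visits by day 7. With L above 7, even a visit on the day of discharge comes after day 7.

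**Step 2: share of compliant first visits scored late**

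Late share = min(8, max(0, L − w)) / 8.

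**Step 3: effect on the five-session indicator**

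Points lost = late share × 1/5.

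| L (days) | w = 0: late share; points lost | w = 3: late share; points lost | w = 7: late share; points lost |
|---|---|---|---|
| 0 | 0%; 0 | 0%; 0 | 0%; 0 |
| 3 | 3/8 = 37.5%; 7.5 | 0%; 0 | 0%; 0 |
| 5 | 5/8 = 62.5%; 12.5 | 2/8 = 25%; 5 | 0%; 0 |
| 7 | 7/8 = 87.5%; 17.5 | 4/8 = 50%; 10 | 0%; 0 |
| 10 | 8/8 = 100%; 20 | 7/8 = 87.5%; 17.5 | 3/8 = 37.5%; 7.5 |

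Under these assumptions the loss cannot exceed 100% × 1/5 = 20 points. A tolerance reduces the effect or, for short stays, removes it. It does not bring the two clocks together: at w = 7 the effect returns once L exceeds 7.

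**Step 4: the same check with contacts scored from discharge**

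A first visit made 0 to 7 days after discharge is on time at week 1 for every L, so the late share among compliant first visits is 0 whatever the stay.

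**The case against.** The best defence is that the scoring clock is stated consistently. Data collection ties adherence monitoring to weeks after the attempt, Study interventions gives the same clock, and the Implementation definition repeats the same contact points. The discharge rule is an operating deadline for consent and start of care; it does not define on time. This stands. A reader might infer that the indicator has two competing definitions, but the text does not support that. What remains is that the operating deadline is looser than the week-1 point used for scoring.

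Study interventions also says that the CHO visits during the week after the nurse's report is passed on. If that report follows soon after presentation, most first visits would fall near week 1. That may be so in practice, but the sentence names no start date and does not override the explicit discharge rule.

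A reader might take the late shares of 37.5% to 100% as the effect on the indicator. They apply to first visits only, and the indicator covers five sessions.

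A reader might also see a second conflict over the end of follow-up, because the Introduction has contacts "and then continue periodically over the immediate 11-week period afterward", which could mean 11 weeks from discharge or from the first visit. This is loose introductory wording, and the methods sections give an explicit last contact at 11 weeks after the attempt. It merits tidying but is not a separate fault.

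Finally, the flowchart is not shown, and visit windows are commonly left to a fuller document. No finding is made of a missing window. A window sets how late is late; it does not settle which date the weeks are counted from.

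**Conclusion.** The mismatch is real and minor. A first visit that meets the discharge rule can be late on the post-attempt schedule after any stay of at least one day if no tolerance applies, and always is when the stay exceeds seven days. The Table 1 on-time proportion therefore partly reflects length of stay.

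The size cannot be known from the article. Under the assumptions listed, it is about 7.5 points of the indicator at a three-day stay and 17.5 at a seven-day stay with no tolerance, and 0 and 10 points with three days' tolerance. If a late first visit also pushes back later contacts, the effect would be larger; if CHOs usually visit soon after discharge, it would be smaller.

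It would be wrong to infer that the go/no-go decision or the effectiveness result is at risk. The implementation indicators are reported descriptively, none of the Table 2 progression criteria concerns timeliness, and the re-attempt comparison does not use visit timing.

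**What to change.** Put the visit rule and the adherence score on the same clock for all five contacts. One workable choice is to score contacts at 1, 2, 4, 7 and 11 weeks from discharge, using the discharge date already sent to the research team. Align the Introduction, Study interventions, Recruitment & Retention, the Implementation definition under Outcomes, and Data collection. State in the Introduction which date the 11 weeks run from.

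Label the date in the nurses' record book as the attempt date or the presentation date, and report on-time delivery on the post-attempt clock as a sensitivity result.

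The cost is a few aligned sentences and at most one date field, since visit and discharge dates are already captured. The article describes recruitment and follow-up as ongoing, so the scoring rule can be set before analysis. The small downside is that the main figure would depart from the post-attempt timing of the cited contact schedule; the sensitivity result keeps that comparison.
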